### Data management

The vFCR encounter through the ExtendedCare platform is HIPAA compliant and is not recorded. Survey and demographic information collected from participants will be deidentified, collected through REDCap [27], and managed by trained research staff at the study site. Qualitative interviews will be recorded, transcribed, and reviewed by the study team for accuracy. Digital audio recordings, transcriptions, and study notes will be stored on a secure password-protected HIPAA-compliant share drive available to researchers at the study site. Transcribed qualitative interviews will exclude identifiable information to protect participant privacy.

### Statistical methods

For all feasibility objectives outlined above in the “Feasibility Objective Outcomes” section, we will report proportions and exploratory outcome estimates with 95% confidence intervals (CI), consistent with SPIRIT recommendations [17], using Wilson score intervals for proportions. For the FCR caregiver attendance exploratory outcome, to account for variation in the duration of patient hospitalizations and thus the number of FCR encounters, we will report the duration-weighted mean for the FCR caregiver daily attendance proportion using Poisson regression with offset term based on the number of weekdays and with confidence intervals adjusted for clustering at the family-level. Similarly, for the medical error exploratory outcome, we will estimate adjusted rates using Poisson regression with offset term based on the total length of stay.

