### Intervention

During daily rounds, a computer mounted on a medical grade pole with wheels and an omnidirectional microphone, a speaker, and a video camera will be taken on rounds to conduct the telehealth visits during vFCR. Our study site utilizes Health Insurance Portability and Accountability Act (HIPAA) compliant software called ExtendedCare for telehealth visits; this software launches directly from the patients’ chart in the EHR and integrates with the video medical interpreting platform, Martii. During rounds, the NICU team will launch the application and send a link to the vFCR through ExtendedCare by the participant’s preferred mode of communication (text or email). The link connects the parent directly to vFCR and does not require an additional download or application to use. A video interpreter will be invited to the vFCR when the parent is present. FCR rounds will then proceed with the NICU team. Parents of enrolled participants are not required to participate in vFCR and can join vFCR as frequently as they desire, come to the bedside for in-person FCR, or not participate in rounds at all. If there are technical difficulties, a help desk is available 24 hours per day, 7 days per week for the ExtendedCare application.

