### Feasibility objective outcomes

We will test the feasibility of conducting a trial for vFCR in NICU patients with LOE parents. Feasibility will be assessed through the following objectives (Table 2):Objective 1 (primary feasibility objective) will measure the reach of vFCR for LOE families and will be met if at least 75% of enrolled families have at least one parent who subscribes to use vFCR.Objective 2 will monitor uptake of vFCR and will be met if at least 70% of enrolled families use vFCR at least once during their infant’s hospitalization. We will measure the percent of enrolled families that participate in vFCR by tracking logins to the ExtendedCare application that is used for parent-to-provider video access during vFCR.Objective 3 will measure the fidelity the intervention and will be met if at least 95% of vFCR with a parent in attendance whose language preference is other than English includes a professional medical interpreter in the parent’s preferred language.Objective 4 will measure the technical feasibility and will be met if at least 90% of vFCR encounters have no technical issues. This will be assessed using vFCR observations, parent solicited reports, and reviewing the hospital helpdesk technical issues log during the study period.Objective 5 will assess the feasibility of survey data collection with a goal of survey response rates being at least 75% and with missingness for each variable of interest being less than 10%.

**Table 2 Tab2:** Feasibility objectives

Objectives	Indicator	Criteria for success
*Feasibility* of reach of vFCR	At least one LOE parent subscribes to vFCR	Subscription of at least one parent to vFCR will be at least 75% among LOE-enrolled families
*Feasibility* of uptake of vFCR	Use of vFCR during the trial period	Parent use of vFCR at least once will occur among at least 70% of enrolled families
*Feasibility* of intervention fidelity	Interpreter use for vFCR encounters with a parent in attendance with LOE	Use of a professional interpreter will occur in at least 95% of vFCR encounters that have a LOE parent in attendance
*Feasibility* of technology	Technical issues	Among attempted vFCR encounters, at least 90% will have no technical issues
*Feasibility* of data collection	Survey response for survey-derived outcome	Survey response rate will be at least 75%; all data elements will have less than 10% missing values

*vFCR* virtual family-centered rounds, *LOE* language preferred other than English

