### Data collection

Data collection will be ongoing and include daily weekday vFCR observations, parent surveys, and reviews of the EHR and technical issues log. Adherence to the feasibility objectives will be monitored. For objective 1, we will use daily chart review to track the number of LOE-eligible infants indicated by preferred language in the infant chart and calculate the percentage subscribed based on this total number. If the preferred language is not listed, research coordinators will cross-reference notes in the medical record for admitted patients in the NICU to determine the language preferences of the family. For objective 2, we will track logging in to the ExtendedCare application for subscribed families to determine the percentage that access the technology. Encounters will be measured using a dichotomous rating among the vFCR encounters with a LOE parent(s) in attendance of whether the FCR encounter includes the presence of the professional medical interpreter for objective 3. Objective 4 will be assessed using FCR observations, parent-solicited reports, and helpdesk technical issues log. Objective 5 will be assessed by survey response rates and by missing data elements for each variable of interest.

Data collection for exploratory outcomes will be collected primarily through several methods. FCR parent attendance is collected by the NICU rounding team during weekday rounds where a data collection sheet is marked if a parent joins FCR. EHR review will be used at discharge to measure length of stay and any human milk feeding. Medical errors and adverse events will be reviewed by comparing EHR data with the study site’s internal incident reporting system along with solicited reports, as previously described in the vFCR pilot study [5].

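### Objectives 3 and 4 pool repeated encounters within families, so the planned Wilson intervals will be too narrow under any positive within-family correlation, by an amount the protocol does not let us fix

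*Protocol article*

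**What the plan says.** The interval rule in Statistical methods opens with "For all feasibility objectives outlined above in the" feasibility section and continues "we will report proportions and exploratory outcome estimates with 95% confidence intervals (CI), consistent with SPIRIT recommendations [17], using Wilson score intervals for proportions". It therefore reaches all five objectives.

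Two of them have the encounter as their unit:

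- **Objective 3**, in Table 2: "Use of a professional interpreter will occur in at least 95% of vFCR encounters that have a LOE parent in attendance". Data collection confirms a yes/no rating for each encounter: "Encounters will be measured using a dichotomous rating among the vFCR encounters with a LOE parent(s) in attendance".
- **Objective 4**, in the text, "will be met if at least 90% of vFCR encounters have no technical issues"; and in Table 2, "Among attempted vFCR encounters, at least 90% will have no technical issues".

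Encounters repeat within families. Study overview offers subscribers a link every weekday except university holidays, and Intervention says that parents "can join vFCR as frequently as they desire".

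The only mention of clustering is the next sentence of Statistical methods. There the exploratory attendance outcome is to be reported "with confidence intervals adjusted for clustering at the family-level".

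**The concern.** The Wilson interval is derived for independent binary observations. That fits Objectives 1 and 2 (one result per family) and the Objective 5 response rate (one surveyed parent per family). It does not fit a pool of encounters in which a few families with long stays may supply much of the denominator. Encounters of one family share at least the family's language, and so the availability of an interpreter in that language. Positive correlation is the natural expectation.

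The protocol handles this nesting for an exploratory outcome and leaves it out for two prespecified success criteria. What is at stake is the stated uncertainty of interpreter fidelity and technical reliability, two results that another site or a later trial would want to use. An interval that ignores clustering can exclude values, such as interpreter use below 90%, that the data do not rule out.

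**Working it through.** **1. The protocol's own precision figure.** Sample size gives n = 36 and a margin of at most 16.3 points for Objectives 1, 2 and 5. The Wald half-width at p = 0.5 is 1.96 × √(0.25/36) = 16.3 points; the Wilson half-width is 15.5. The figure reproduces. It concerns family-level proportions only, so clustering does not touch it. No precision is stated for Objectives 3 and 4.

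**2. Inputs for Objectives 3 and 4.**

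- Families using vFCR: the Objective 2 target applied to the planned sample, 0.70 × 36 = 25.2, rounded up to 26.
- Not in the article, so assumed over a range: mean encounters per using family m = 3 to 20; within-family ICC = 0.01 to 0.3; use either equal across families or uneven, with a coefficient of variation (CV) of about 1.

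**3. Interval width.** Design effect DE = 1 + [(1 + CV²)m − 1] × ICC, and effective n = N/DE. Take m = 10, so N = 26 × 10 = 260, with uneven use (CV = 1):

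- ICC 0.1: DE = 1 + (20 − 1) × 0.1 = 2.9; effective n = 260/2.9 = 89.7.
- ICC 0.3: DE = 1 + (20 − 1) × 0.3 = 6.7; effective n = 260/6.7 = 38.8.

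Wilson intervals at an observed 95%:

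| Basis | n used | 95% interval |
|---|---|---|
| Pooled encounters, as planned | 260 | 91.6 to 97.1% |
| DE 2.9 | 89.7 | 88.4 to 97.9% |
| DE 6.7 | 38.8 | 83.3 to 98.6% |

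At the mild end the effect vanishes. With equal use, m = 3 and ICC 0.01, DE = 1 + 2 × 0.01 = 1.02, and the interval widens by about 1%. Across the equal-use grid (m = 3 to 20, ICC 0.01 to 0.30) the adjusted interval is 1.01 to about 2.7 times as wide.

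**4. Coverage of the planned interval.** Beta-binomial simulation, 26 families, true proportion 95%:

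| Mean encounters per family | ICC | Use | Coverage of nominal 95% |
|---|---|---|---|
| 3 | 0.02 | uneven | about 95% |
| 5 | 0.01 | uneven | about 94-95% |
| 5 | 0.05 | uneven | about 91-92% |
| 10 | 0.1 | equal | about 83% |
| 10 | 0.1 | uneven | about 78-79% |
| 10 | 0.3 | uneven | about 58% |
| 20 | 0.1 | uneven | about 65% |
| 20 | 0.3 | uneven | about 44% |

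Results at a true 90% are similar. More families do not cure it: with 36 families, m = 10, ICC 0.1 and uneven use, coverage is still about 78%.

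**5. Effect on the success criteria.** Both criteria compare the observed percentage with a threshold (95% and 90%). No confidence limit enters, and clustering does not change the observed percentage. The met or not-met results are the same under either interval.

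**The case against.** The case for leaving the plan alone has real substance.

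- **Consequence.** Neither objective is primary, neither is judged on a confidence limit, and no precision figure is stated for them. A reader might infer that two of the five feasibility verdicts are compromised. The criteria do not support that; only the interval printed beside each percentage is affected. This stands.
- **Size.** A reader might also infer that the intervals are bound to be far too narrow. Objective 2 counts a family as a user after one use, so encounter counts may be low, and with a small ICC the loss is negligible. The article gives no inputs that settle the matter. This stands: the direction is sound under positive correlation, the amount is not known.
- **Source of the correlation.** Nothing says that a family keeps the same device, connection or rounding team. Intervention describes one platform, one integrated interpreter service and equipment taken round the unit. Failures from those sources could be shared across families on the same day, which family clustering would not capture. This limits what the fix achieves but does not make encounters independent.
- **Room in the wording.** The article does not say which n enters the Wilson formula, and an unseen analysis plan could specify an effective one. This is weak: the rule is stated for all feasibility objectives, and clustering is named only for attendance in the sentence that follows.

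**Conclusion.** The point holds as a should-fix on reported precision. The stated rule gives Objectives 3 and 4 an interval that assumes independent encounters, and that interval is too narrow under any positive within-family correlation. The shortfall could be trivial or severe: coverage from about 95% down to about 44% over the assumed range, with 78-83% at the middle values of 10 encounters per family and ICC 0.1. These figures rest on assumed ICCs, encounter counts and unevenness of use, and on 26 using families. Point estimates, the success calls, the primary objective and the 16.3-point statement are all unaffected.

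**What to change.** Amend the sentence in Statistical methods as follows.

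1. Keep Wilson intervals for Objectives 1 and 2 and for the Objective 5 response rate.
2. For Objectives 3 and 4, report a 95% interval with family as the cluster and a small-sample correction. One option is Wilson on an effective sample size, p(1 − p) divided by the corrected family-clustered variance, with a t quantile on families minus 1.
3. State a fallback for no failures, or too few to estimate the clustered variance. With none, the effective sample size is 0/0. One option is Wilson with the number of contributing families as a conservative effective n. If all 260 encounters of 26 families succeed, the lower limit is then 26/(26 + 1.96²) = 87.1%, against 260/(260 + 1.96²) = 98.5% on pooled encounters.
4. Print the number of families and the encounters per family beside each proportion.

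The cost is a few sentences and a few lines of code, with no new data. The intervals become wider, and coverage may still fall short at high ICC: in simulation the effective-sample-size interval covered about 88% (10 encounters, ICC 0.3) and 86% (20 encounters, ICC 0.3), against about 58% and 44% for the planned interval.

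### Objectives 3 and 4 count repeated encounters within families, so the plain Wilson intervals specified for them will be too narrow if encounters in the same family are positively correlated

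*Protocol article*

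**What the plan says.** The Statistical methods section sets the scope and the method in one sentence. The scope is "For all feasibility objectives outlined above in the “Feasibility Objective Outcomes” section, we will report proportions"; the method is 95% intervals, "consistent with SPIRIT recommendations [17], using Wilson score intervals for proportions". No feasibility objective is exempted.

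The units of the objectives differ (Feasibility objective outcomes, Table 2):

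- Objective 1 counts families: "at least 75% of enrolled families have at least one parent who subscribes to use vFCR". Objective 2 also counts families. Objective 5 rests on one surveyed parent per family (Data collection).
- Objective 3 counts encounters: "Use of a professional interpreter will occur in at least 95% of vFCR encounters that have a LOE parent in attendance".
- Objective 4 counts encounters: "Among attempted vFCR encounters, at least 90% will have no technical issues".

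The Data collection section confirms a yes/no rating per encounter for Objective 3. Under Study overview and Intervention, subscribed parents receive a link every weekday and may join as often as they wish, so the number of encounters per family has no limit.

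For one other outcome, exploratory attendance at rounds, the same Statistical methods paragraph reports results "with confidence intervals adjusted for clustering at the family-level".

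**The concern.** A Wilson score interval treats its n observations as independent. For Objectives 3 and 4, n is a number of encounters, and these come in runs from the same family. A family's preferred language, and with it the supply of interpreters, stays the same from day to day; its device and connection probably do too. These are natural causes of a missing interpreter or a technical failure. Positive correlation within families makes the effective sample size smaller than the encounter count, so an interval labelled 95% covers the true proportion less often than that.

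The article recognises this dependence for attendance, which has the same repeated-rounds structure, but names an independent-observations interval for two formal objectives. This is a stated method, not a detail left to an analysis plan. At stake is the uncertainty attached to fidelity and technical feasibility. The trial does not test efficacy, so estimates with intervals are its main quantitative product, and anyone planning a later trial would rely on them.

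**Working it through.** **The plan's own figure.** The Sample size section gives margins of at most 16.3 percentage points at n = 36 for Objectives 1, 2 and 5. The Wald half-width at p = 0.5 is 1.96 × √(0.25/36) = 0.1633, which reproduces it. The Wilson half-width is 15.5 points, also within the stated bound. The statement makes no precision claim for Objectives 3 and 4.

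**Inputs from the article.** Confidence level 95%; targets 95% and 90%; 36 families. Objective 2's 70% target gives 0.70 × 36 ≈ 25 families using vFCR; Objective 1's 75% gives 0.75 × 36 = 27.

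**Inputs assumed.** Encounters per family (m), their variability (coefficient of variation, CV) and the ICC are not in the article, so ranges are shown.

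**Design effect.** With equal counts, DE = 1 + (m − 1) × ICC. With unequal counts, DE = 1 + ((1 + CV²) × m − 1) × ICC. The interval widens by roughly √DE.

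**Mid case: 25 families, m = 10, ICC 0.10.** N = 250, DE = 1 + 9 × 0.10 = 1.9, effective n = 250/1.9 = 131.6. The Wilson interval is [p + z²/2n ± z√(p(1 − p)/n + z²/4n²)] / (1 + z²/n).

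| Objective, observed value | Plain, n = 250 | Effective n = 131.6 | Ratio of half-widths |
|---|---|---|---|
| 3, 95% | 91.6-97.1% | 89.8-97.6% | 1.40 |
| 4, 90% | 85.7-93.1% | 83.7-94.0% | 1.38 |

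**Coverage of the plain 95% Wilson interval.** Beta-binomial simulation, 25 families, 20,000 runs. Each cell shows equal counts / geometric (very unequal) counts.

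| True p | m | ICC 0.02 | ICC 0.10 | ICC 0.30 |
|---|---|---|---|---|
| 0.95 | 5 | 95.5 / 93.8% | 92.7 / 88.1% | 84.3 / 75.9% |
| 0.95 | 10 | 94.3 / 90.9% | 86.8 / 79.0% | 71.8 / 60.1% |
| 0.90 | 5 | 95.7 / 93.3% | 92.7 / 87.3% | 84.5 / 73.8% |
| 0.90 | 10 | 93.7 / 91.0% | 85.5 / 77.7% | 69.7 / 58.1% |

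With ICC 0 and m = 10 at p = 0.95, coverage is 95.9 / 95.3%, so the shortfall comes from the correlation and not from the Wilson method.

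**A second setting: 27 families, CV 0.8, p = 0.95.** At mean 4 and ICC 0.02, coverage is about 94%. At mean 8 it is about 88% at ICC 0.05 and 66-67% at ICC 0.30. The matching design effects at mean 8 are 1 + (1.64 × 8 − 1) × 0.05 = 1.6 and 1 + (1.64 × 8 − 1) × 0.30 = 4.6, so intervals should be about 1.3 to 2.2 times as wide.

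**The case against.** The strongest reply is that nothing decisive depends on these intervals. Table 2 sets success as an observed percentage against 95% or 90%, and no criterion uses a confidence limit. Neither objective is primary, and the precision claim in the Sample size section leaves both out. This stands, and it limits the importance of the point. A reader might infer that an objective could be wrongly declared met; the documents do not support that.

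The reply also notes that no ICC or encounter count is given. The cart, software and interpreter platform serve all families, so they do not by themselves create correlation within a family. With few encounters and a low ICC the shortfall is negligible. This stands too, and the conclusion is therefore conditional.

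Three further inferences are tempting and should not be drawn:

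- That one long-stay family could push the estimate outside its own stated interval. A Wilson interval always contains its observed proportion; the fault is under-coverage of the true proportion.
- That the medical-error model has the same defect. The article says only that "for the medical error exploratory outcome, we will estimate adjusted rates using Poisson regression with offset term based on the total length of stay". It introduces this as similar to the family-clustered attendance model, and a robust variance may be left to the analysis plan.
- That twins seriously distort the human-milk proportions. With 4 twin pairs among 36 families (an assumed number) and perfect correlation within pairs, the design effect is about 1.2, so intervals widen by at most about 10%. The outcome is exploratory.

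The reply does not remove the core: the article names an independence-based interval for proportions whose unit is a repeated encounter.

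**Conclusion.** The point holds for Objectives 3 and 4 only, and on condition that encounters within a family are positively correlated. That is plausible but not documented. For 25 to 27 families with a mean of 4 to 10 encounters and ICC 0.02 to 0.30, coverage of the nominal 95% interval starts at about 94% or slightly higher in the mildest settings. It falls to about 66% at a mean of 8 with ICC 0.30, and to about 60% at a mean of 10 with ICC 0.30 and very unequal counts. Every figure depends on assumed encounter counts and ICC.

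The point estimates, the met/not-met results, Objectives 1, 2 and 5, and the n = 36 rationale are unaffected. The plan should be corrected before analysis, but this is not a fault that undermines the trial.

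**What to change.** Keep plain Wilson intervals for Objectives 1, 2 and 5. For Objectives 3 and 4, keep the encounter-weighted proportion, since that is what Table 2 judges, and replace the interval with a family-clustered one. Either of these would do:

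- A Wilson interval on the effective sample size implied by the family-clustered variance, with a t quantile on families minus 1 degrees of freedom. The correction matters: without it, simulated coverage at p = 0.95 (27 families, mean 8, CV 0.8) is 93.8% at ICC 0.05 and 86.0% at ICC 0.30. That is much better than plain Wilson but still short.
- An intercept-only GEE with an independence working correlation and a small-sample robust variance. An exchangeable working correlation would shift weight away from the encounter-weighted percentage.

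State a fallback for an observed 100%, which is possible near a 95% target and leaves the clustered variance at zero. One choice is Wilson with the number of families as n. With 25 families the lower limit is 25/(25 + 3.84) = 86.7%, against 250/(250 + 3.84) = 98.5% for 250 encounters treated as independent.

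Report the number of families and the distribution of encounters per family beside each result.

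The cost is a sentence or two in the methods and a few lines of code, with no new data. The downside is wider reported intervals.
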